#### Resistance training

Resistance training sessions will involve a progressive combination of activities including: I) mobilization and warm-up (range of motion exercises for the neck, shoulders, arms, trunk, and legs); II) a lower-body strength exercise (sit-to-stand); III) an upper-body strength exercise (seated curl to press exercise with a free-weight load like a pair of water bottles); IV) balance (one-leg standing balance); and V) calm down (stretching and relaxing exercises). Additional file 1 shows this in more detail. During hospital stay, a supervised face-to-face session will take place for the adequacy of the post-surgery exercise. Following the advice of our surgical team, the lower-body strength exercise (i.e., sit-to-stand exercise) will be replaced by a seated knee extension exercise in order to avoid excessive intra-abdominal pressure during the 4 weeks following surgery [see Additional file 2]. Overall, patients will be advised to complete all movements in a slow and controlled fashion during the first two weeks of the program and the 4 weeks after surgery. Then, patients will progress to complete the concentric phase (muscle shortening) as fast as possible, followed by a controlled, slower eccentric phase (muscle lengthening) to maximize mechanical power output and motor unit recruitment (i.e., power training) [53]. Besides, patients will be trained to avoid Valsalva's maneuver during exercise execution.

#### Endurance training

Endurance training sessions will consist of brisk walking (i.e., walking faster than habitual gait speed). Patients will be instructed to walk at a pace that hinders them from talking comfortably, but that allows them to maintain a conversation (i.e., the equivocal stage of the talk test) [54]. Several studies have suggested that the equivocal stage of the talk test is a valid indicator of the ventilatory threshold [55]. Patients will walk independently or assisted (e.g., with the help of other person, a walker, or a walking stick). Overall, endurance training sessions will aim to accumulate at least 30 minutes of continuous or interval brisk walking.

#### Inspiratory muscle training (IMT)

A specific device for IMT (POWERbreathe Medic Plus, Southam, United Kingdom) will be used. Patients will complete 30 repetitions twice a day with a starting load (i.e., intensity) corresponding to the 40% of patient’s maximal inspiratory pressure (PI_max_, see inspiratory muscle function section below for more details), measured at baseline and 1, 3, and 6 months after surgery. For every repetition, the patients will be instructed to exhale until achieving residual volume and will then perform a maximal inspiration (i.e., as fast and for as long as possible) through the IMT device. If needed, patients will be allowed to include a brief rest (30 to 60 seconds) every 5 to 10 repetitions. IMT sessions will be completed twice a day, once after the corresponding resistance or endurance training session, when applicable.

#### Exercise progression

The exercise program will be continuously adapted to the patient’s clinical status and functional capacity. Exercise progression regarding resistance and balance exercises will be achieved by adjusting the number of repetitions, the number of sets, the usage of additional weights and/or by exercise selection (i.e., moving from simple to more advanced exercises). Patients will rate each exercise intensity and overall training session intensity through the Borg’s Perceived Exertion Category-Ratio Scale 1-10 (RPE_1-10_) for aerobic exercise and the OMNI-Scale for resistance training [56, 57]. After a conditioning phase, resistance training prescription will be tuned weekly to target an intensity ranging between moderate to vigorous (i.e., 5- “strong”- to 7- “very strong”- points RPE_1-10,_ respectively). For guidance, if the patient complies with the exercise prescription, the training volume will be increased (i.e., higher number of repetitions and/or sets) or a more complex exercise will be selected based on the established criteria (Table 1). In contrast, scoring more than 8 points RPE_1-10_ will be considered a regression criterion, which entails a decrease of 2-3 repetitions per exercise and/or selecting an easier exercise. On the other hand, endurance exercise will range from 10 minutes (starting level of group I of disabled patients) to 60 minutes per session, while exercise progression will be set according to the establish criteria (Table 1). Accordingly, if the RPE_1-10_ for endurance training session exceeds 8 points, session duration will be reduced by 5 minutes. In terms of IMT, the patients will be instructed to increase the load of the threshold device between 0.5 and 1 levels (i.e., 3.5 and 7 cm H_2_O) every week if being able to complete twice a day 30 repetitions. If return to exercise/usual activities is delayed due to post-operative complications, study participants will continue in the study and restart the exercise intervention once they are able until completing the 12 weeks of training.

**Table 1 Tab1:** Training regression and progression criteria

**Starting level (SPPB score)**	**RESISTANCE TRAINING**						**ENDURANCE TRAINING**
	Lower body		Upper body		Balance		Brisk walking
	**Sets**	**Repetitions**	**Sets**	**Repetitions**	**Sets**	**Time (s)**	**Time (min)**
**A (0-3)**	1 - 3	3 - 5	1 - 3	3 - 5	3	3 - 5	10 - 15
**B (4-6)**	2 - 3	5 - 8	2 - 3	5 - 8	3	3 - 5	15 - 20
**C (7-9)**	2 - 3	8 - 10	2 - 3	10 - 15	3	3 - 5	20 - 25
**D (10-12)**	3	10 - 12	3	10 - 12	3	5 - 10	25 - 30
**E (12)**	3	10 - 15	3	10 - 15	3	10 - 15	≥ 30

*SPPB* Short Physical Performance Battery

#### Adherence and exercise monitoring

Patients will be contacted weekly on a 20-minute telephone support session by the clinical exercise physiologist to report adherence to the home-based training. Thus, every week they will receive an explanation about the purpose of the intervention and the possible benefits of the exercises and progress will be reviewed. Motivation strategies will be used for achieving engagement to sustain exercise activity and/or achieve higher or progressively more intense performance. These strategies are based on the principles of Self Determination Theory [58]. Participants will have the opportunity to discuss any issues related to their exercise program and any barriers to exercise will be taking into consideration. Attendance of each participant will be recorded and reasons for dropouts will be documented.

### Primary outcomes

#### Health-related quality of life

HRQoL will be assessed with the European Organization for the Research and Treatment of Cancer Quality of Life Questionnaire Core 30 (EORTC QLQ-C30) [59]. The questionnaire includes items for the assessment of the global health status, physical, role, cognitive, emotional, and social functioning, as well as assessment items of symptoms and financial difficulties due to cancer and its treatments. Items are assessed from 1 to 4 (1: not at all, 2: a little, 3: quite a bit, 4: a lot) and overall health and the patient's quality of life from 1 to 7 (1 for very poor and 7 for excellent). The total score ranges from 0 to 100 (higher score is considered better). A change of 10 points or more is considered clinically relevant [60]. As complementary questionnaires we will also use the EORTC QLQ-CR29 [61], which includes 29 items specifically aimed at patients with CRC and the EORTC QLQ-ELD14 [62, 63], aimed at elderly patients (≥70 years) with cancer and that includes 14 items.

#### Functional capacity

The Barthel Index [64] will be used to assess the capacity of patients to execute ten basic activities of daily living (i.e., feeding, transferring from bed to chair, using the toilet, bathing/showering, personal hygiene, dressing, walking, stair climbing, and bowel and bladder control). The total score ranges from 0 (total dependence) to 100 (independence) with intervals of 5 points. A change of 5 or more points is considered clinically relevant [65].

### Secondary outcome measures

#### Physical performance

Physical performance will be measured with the SPPB [66], which assesses the patients’ ability to perform three physical tasks: I) static balance, standing for 10 seconds with their feet together (1 point), in semi-tandem, (1 point) and in tandem position (up to 2 points), II) 4-meter habitual gait speed (0 to 4 points), and III) the ability to stand up from a chair during a five-repetition sit-to-stand test (0 to 4 points). The total score ranges from 0 (worst) to 12 (best). Scoring less than 10 points indicates a high risk of frailty, deterioration, and falls [67]. A one-point change in the test is considered clinically relevant [68].

#### Frailty

The presence of frailty will be assessed according to Fried’s frailty phenotype criteria [69], which includes five health-related domains: involuntary weight loss (> 4.5 kg in the last year), weakness (handgrip strength, JAMAR hydraulic hand dynamometer, Nottinghamshire, UK), self-reported exhaustion during the last week, slowness (4.5-meter habitual gait speed test), and low levels of PA (walking less than 2.5 and 2 hours, or an equivalent energy expenditure, for men and women, respectively). Depending on the overall score obtained, participants will be classified into three different categories: frail (≥3 criteria), pre-frail (1 or 2 criteria) or robust (does not meet any criteria).

#### Physical fitness

Patients’ physical fitness will be evaluated through the Senior Fitness Test, a battery of tests designed for the community-dwelling elderly population [70]. Specifically, this battery assesses the patients’ cardiorespiratory capacity (2-minute step test), strength and flexibility of the lower limbs (30-second sit-to-stand test and chair sit and reach test, respectively) and upper limbs (30-second arm curl test and back scratch test, respectively), balance (Flamingo test), maximal gait speed (10-meter maximal walking test) and agility (Timed-up and go test). A detailed description of each test is available elsewhere [70]. The patient’s score for each capacity will be determined according to the specific normative values (i.e., percentiles) for non-institutionalized Spanish older adults [71].

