
There is still a lack of knowledge on the benefits of exercise in older and more vulnerable patients, who are precisely those with the highest risk of complications and the greater loss of functional independence and HRQoL after CRC treatment. For this reason, we aim to study the effects of an individualized home-based multicomponent exercise program, supervised by a clinical exercise physiologist through telephone calls, on functional capacity and HRQoL in older adults undergoing elective CRC surgery when compared to usual care. Our primary hypothesis is that the exercise program improves functional capacity and HRQoL of older patients with CRC compared to usual care. The secondary aims will be to investigate the effect of the exercise program on physical performance, surgical complications and hospital readmissions, the prevalence of frailty, anxiety and depression, sarcopenia and cancer-cachexia, as well as the effects on physical fitness and inspiratory muscle function in comparison to usual care. Furthermore, the intervention’s safety and feasibility will be studied by registering patient’s adverse events and adherence to the program.

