### Study participants, screening and recruitment

Patients will be screened, informed, and included in the study at the HGUGM, Madrid, Spain. All patients will be provided a written informed consent. CRC patients aged 75 or older will be recruited at the geriatric outpatient clinic after the completion of a comprehensive geriatric assessment (CGA). The trial inclusion criteria will be: I) being 75 years or older, II) confirmed CRC diagnosis, III) being included in the surgical waiting list, and IV) being able to communicate, and able and willing to provide informed consent. The trial exclusion criteria will be: I) dismissal for surgery, II) any active limitation which affects adherence to the study procedures like terminal disease, myocardial infarction, or fractures in any limb (within the last three months before study participation), inability to walk or severe dementia (i.e., scoring Mini-Mental State Examination ≤ 18 points). Patients will be previously informed about the program’s content, study aims and randomization and about the role of care providers and research staff during participation. An overview of the study participant’s flow diagram is shown in Fig. 1.

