#### Exercise intervention

The Consensus on Exercise Reporting Template (CERT) is followed to provide elemental information about the exercise intervention [51]. The exercise intervention will be separated into I) pre-operative phase (prehabilitation), lasting from patient’s enrollment to hospital admission for CRC surgery, II) perioperative phase, from CRC surgery to patient’s discharge from hospital, and III) post-operative phase (rehabilitation), extending up to 12 weeks after CRC surgery. According to leading guidelines on exercise prescription for older adults [52], the exercise program will be tailored to the functional capacity of the patients. Thus, patients will be classified into 4 different groups depending on their Short Physical Performance Battery (SPPB) score, as follows: I) person with disability (SPPB score 0 to 3); II) frail person (SPPB score 4 to 6); III) pre-frail person (SPPB score 7 to 9); and IV) robust person (SPPB score 10 to 12) (see below: *Physical Performance*). The SPPB score will be the decision rule for determining the starting level of the program, which will be reviewed at subsequent face-to-face training sessions by the clinical exercise physiologist. A total of three face-to-face training sessions will be conducted individually at baseline (at own home for adjusting program to the environment of the patient), during hospitalization (once early mobilization of the patient is indicated), and one month after CRC surgery in the hospital setting. In these face-to-face training sessions, the clinical exercise physiologist will provide the corresponding education materials, guidance and motivation to complete the exercise program, observe exercise performance, correct exercise technique, and give feedback to the patients. The educational materials include an informative notebook with the explanations of the exercise program, an exercise diary and audiovisual material. Moreover, patients will receive instructions on how to complete the exercise diary for recording exercise sessions (e.g., exercise modality, repetitions, duration, intensity) of each training session.

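### Scoring each fitness test as a percentile of community norms compresses change in low-functioning patients; the raw test results should be analysed and the percentiles kept for description

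*Protocol article*

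**What the plan says.** Under Physical fitness, the article uses the Senior Fitness Test, described as "a battery of tests designed for the community-dwelling elderly population". It covers step count, chair stands, arm curls, flexibility, balance, maximal gait speed and timed-up-and-go. The score for each capacity is then fixed by reference to norms: "score for each capacity will be determined according to the specific normative values (i.e., percentiles) for non-institutionalized Spanish older adults". No section names repetitions, seconds, centimetres or metres per second as the quantity to be analysed.

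The effect on fitness is a stated secondary aim; the Background lists it among the aims: "as well as the effects on physical fitness and inspiratory muscle function in comparison to usual care". Under Statistical analysis, change in continuous primary and secondary outcomes goes into linear mixed models, and the consistency of the group difference is to be examined by age, frailty, delirium and baseline functional status.

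The Exercise intervention section provides for the whole functional range: "I) person with disability (SPPB score 0 to 3); II) frail person (SPPB score 4 to 6") at the low end and "III) pre-frail person (SPPB score 7 to 9); and IV) robust person (SPPB score 10 to 12") at the high end. Eligibility (Study participants, screening and recruitment) has no frailty requirement: "I) being 75 years or older, II) confirmed CRC diagnosis, III) being included in the surgical waiting list", plus ability to communicate and consent. It excludes patients with "inability to walk or severe dementia".

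**The concern.** A percentile is a non-linear transform of the raw result. It is steep near the middle of the reference population and flat in its tails. The reference population here is non-institutionalised older adults. The trial population is people aged 75 or older awaiting colorectal cancer surgery, some of them frail or disabled, who are tested again in the months after the operation. The Background itself says that physical function usually stays below baseline for three to six months after treatment. Some observations are therefore likely to fall in the lower part of the norms, where a given change in repetitions or seconds moves the percentile less.

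Two things follow. The fitness comparison may lose power. And a comparison of effects between frail and fitter patients would partly reflect the shape of the scale. The second matters because the article's rationale is to learn whether older, more vulnerable patients benefit.

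**Working it through.** **The plan's own figure.** The only sample-size calculation is for the QLQ-C30: difference 10, SD 23, two-sided 5%, power 80%. Then n per arm = 2 × (1.960 + 0.842)² × 23² / 10² = 83.0, rounded up to 84, or 168 in total. The article states 166, which agrees closely. It has no bearing on fitness, for which no calculation is given. It is used below only to set the size at 166 / 2 = 83 per arm.

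**Assumptions not in the article.** Norms are normal; z is a patient's position in norm SDs; the percentile is 100 × Φ(z). The cohort's SD equals the norm SD. The cohort's mean position is unknown and is varied.

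**Step 1: what one raw change is worth.** Gain in percentile points = 100 × [Φ(z + δ) − Φ(z)]; a loss is the same with −δ.

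| Start z | Gain of 0.3 SD | Loss of 0.3 SD | Gain of 0.5 SD |
|---|---|---|---|
| 0 | 11.8 | 11.8 | 19.2 |
| -1 | 8.3 | 6.2 | 15.0 |
| -1.5 | 4.8 | 3.1 | 9.2 |
| -2 | 2.2 | 1.2 | 4.4 |
| -3 | 0.2 | 0.1 | 0.5 |

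**Step 2: power.** Simulation with 83 per arm, baseline-to-follow-up correlation 0.6 and a t-test on change. The SD of change is √(2 × (1 − 0.6)) = 0.894 norm SD. The effect is 0.44 of that, or 0.394 norm SD, chosen to give 80% power on raw scores.

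| Cohort mean | Raw | Percentile | Percentile, table stopping at P5 |
|---|---|---|---|
| 0 | 80% | 76% | 76% |
| -1 SD | 80% | 75% | 73% |
| -1.5 SD | 80% | 70% | 65% |
| -2 SD | 80% | 61–62% | 52% |

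About 4 of the 5 points lost at -1 SD are lost already with the cohort at the norm mean. Lying 1 SD low adds only about one more point.

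**Step 3: subgroups.** Every patient gets the same raw effect (0.394 norm SD), and the cohort is split at its median baseline. Mean effect in percentile points:

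| Cohort mean | Lower half | Upper half | Ratio |
|---|---|---|---|
| -1 SD | 7.5 | 11.4 | 1.5 |
| -1.5 SD | 4.8 | 9.7 | 2.0 |

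The difference between halves comes entirely from the scale.

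**The case against.** **Position on the norms.** The article gives no baseline distribution and does not say whether the norm tables are specific to age and sex, or where they stop. Pre-frail and robust patients are eligible, patients who cannot walk are excluded, and fitness is not tested at discharge. A reader might infer that the cohort sits in the tail and that real gains would barely register. The documents do not support that. A cohort mean at -2 SD would put about 64% of patients below P5, which is hard to assume for a cohort that includes robust patients. This objection stands and limits the size of the point.

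**The analysis variable.** The article says how the score is determined. It does not say that raw results are discarded, and the full analysis plan is not shown. This stands only in part: the percentile is the one score the article defines, and the mixed models are applied to continuous secondary outcomes. As written, the percentile is what is analysed.

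**Raw is not always better.** Timed tests can be right-skewed. With log-normal times (log-SD 0.4, an assumption) and a proportional effect, raw seconds gave 72% power against 76% for percentiles at -1 SD. The order reversed at -1.5 SD (72% against 70%) and at -2 SD (71% against 63%). Percentiles also put tests in different units on one scale, and raw tests have floors of their own, such as zero chair stands. The skewness point is met by a transformation. The loss of a common scale is a real but small cost, and the floors remain.

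**Subgroups.** The article does not say which outcomes the subgroup checks cover. A reader might also infer an artificial absence of effect in frail patients. The calculation shows attenuation, not absence.

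**Conclusion.** The point holds in limited form. The article fixes a score on which equal physical changes count for less in patients low on the norms, while it enrols such patients and plans comparisons by frailty and baseline function. Under normal norms, 83 per arm and 80% power on raw scores, the cost is about 5 points of power with the cohort mean at -1 SD and about 10 at -1.5 SD, with larger losses only near -2 SD. A uniform raw benefit can look 1.5 to 2 times larger in the fitter half with the cohort mean between -1 and -1.5 SD. All of this depends on the cohort's position, which the documents do not give.

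Physical fitness is one of several secondary outcomes. The primary outcomes are not percentile-scored, and the SPPB keeps its own 0 to 12 scale, so the trial's main conclusions are not at risk. The change is nonetheless worth making, because it is cheap and it removes a scale artefact from the frailty comparison.

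**What to change.** State under Physical fitness that the outcome for each Senior Fitness Test item is its raw result (repetitions, seconds, cm or m/s), with a log or speed transformation fixed in advance for skewed timed tests. Use these values in the mixed models and in any subgroup comparison of fitness. Keep the Spanish percentiles to describe the cohort.

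The cost is a change of wording. The raw value has to be recorded before a percentile can be looked up, so no measurement or visit is added. The one downside is that the tests no longer share a single scale; reporting the percentiles descriptively beside the raw results covers most of that.

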#### Physical activity

Changes in PA will be determined through the Physical Activity Scale for the Elderly (PASE) questionnaire [72]. Briefly, this questionnaire evaluates the level of self-reported physical activity including occupational, household and leisure activities over the past 7 days in individuals aged 65 years and older. The total PA is computed on an overall weighted score (from 0 to more than 400 points) where the minimal clinically important difference for cancer patients ranges between 17 and 25 points [73]. Current evidence supports the PASE as the best questionnaire for measuring moderate to vigorous PA in older adults [74].

#### Sarcopenia and cachexia

Changes in muscle mass and quality will be recorded by ultrasound examination (Lumify system and L12-4 linear array transducer, Philips Ultrasound, WA, USA) of the lower and upper limbs. Patients will lie on an examination table in supine position with a foam roller placed beneath the knees (i.e., with slight knee flexion). After allowing 10 minutes for fluid stabilization, three cross-sectional images of the rectus femoris (at 50% of the distance between the anterior superior iliac spine and the proximal border of the patella) and biceps brachii muscles (at 66% of the distance between the acromion process and the elbow crease) will be acquired to determine muscle thickness and echo-intensity (i.e., grayscale quantification). In addition, three longitudinal images of the vastus lateralis muscle (at 65% of the distance between the greater trochanter and the distal boundary of lateral femur condyle) with the probe aligned with the fascicle plane will be acquired to determine muscle thickness and architecture (i.e., fascicle length and pennation angle). The image acquisition location and skin landmarks will be transferred to an acetate template to improve measurement reliability of the following visits. All images will be subsequently analyzed using Fiji image analysis software [75] and the Simple Muscle Architecture Analysis tool for Fiji [76]. The determination of low levels of muscle mass, necessary for the diagnosis of sarcopenia, will be determined using the cut-off points for the Ultrasound Sarcopenia Index, which is obtained by the ratio between fascicle length and muscle thickness [77]. The operational definition of sarcopenia revised by the European Working Group on Sarcopenia in Older People and the corresponding cut-off points will be applied for the diagnosis of sarcopenia [78]. In addition, the presence of cancer-cachexia will be evaluated according to the international consensus for the definition and classification of cachexia associated with cancer [79].

